### Participant identification

The principal investigator and all co-investigators undertake to keep the identities of the patients who participate in the study confidential, by assigning a coded identifier to each patient.

This patient identifier will be present on all eCRF pages and all attached documents (reports of imaging studies, laboratory tests, health economics analysis, etc.). It will be the only information allowing retrospective connection of the data to the patient.

The coded identifier will be the first letter of the patient’s first name, the first letter of the patient’s surname, the birth year of the patient, and the study inclusion number, in that order.

## Statistics

### Description of planned statistical methods, including planned intermediate analysis schedule

Statistical analyses will be performed by a biostatistician from the methodology and biostatistics platform using SAS or R or Stata.

A data review will be carried out before the freezing of clinical trial data bases, and statistical analyses, with the main stakeholders in the study (investigator, CRA, data manager and biostatistician…). The objective of this review will be to take stock of any difficulties encountered during the study, and to classify the different deviations in order to define the analysis populations.

The statistical analysis will be conducted according to a pre-defined plan.

**Description of the groups at baseline**

Baseline characteristics will be studied using descriptive statistics. No statistical tests will be performed.

**Analysis of primary endpoint**

Lowest oxygen saturation, measured by Masimo Rad7 oximeter, during the interval between the first laryngoscopy (defined as introduction of the laryngoscope into the mouth) and the end of the second minute after successful ETI (32) will be compared between groups using linear mixed-effect regression model to take into account stratification variable (centre as random effect, intubator status (expert or non-expert) and preoxygenation device as fixed effect).

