# Justification of the study

## Positioning of the study

Endotracheal intubation (ETI) is a common procedure in ICUs (1). The risk factors in ICU patients result in a high complication rate (up to 50%) (2). Severe complications are severe hypoxaemia (25%), severe hypotension (25%), cardiac arrest (1-3%), and death (0.5-3%) (1,3,4). Risk factors for potentially fatal hypoxaemia are hypoxaemia before ETI and/or difficult ETI (5). Hypoxemia during ETI is associated with cardiac arrest occurrence (3,6) and morbidity.

Predicting hypoxaemia during ETI is challenging (5). Pre-oxygenation is universally recommended to reduce the risk by prolonging the safe apnoea time (7,8). Pulse oximetry saturation (SpO_2_) is monitored in ICU but only detects late-stage hypoxaemia. FeO_2_ is not available for assessing pre-oxygenation efficacy in the ICU. And this technique has limitations in the emergency setting (sensitivity to leaks) and is not available in ICUs (9). Moreover, in critically ill patients, particularly those with acute hypoxemic respiratory failure, FeO_2_ may not be a reliable measure of the effectiveness of preoxygenation: the reduction in functional lung volume leads, on the one hand, to a reduction in FRC (Fonctional Residual Capacity) and, on the other hand, to a shunt that reduces the efficiency of the alveolar-capillary interface (10). The result is that both SpO_2_ and FeO_2_ can be high while PaO_2_ is low. PaO_2_ can be considered the reference standard for evaluating the effectiveness of preoxygenation but unfortunately cannot currently be obtained at the bedside in real-time in clinical practice (9). Non-invasive ventilation (NIV) is currently recommended for patients with severe hypoxaemia but is associated with a higher risk of severe hypotension (11–15). Last, extended duration of preoxygenation did not help to increase quality of its own (16). Thus, at present, the effectiveness of pre-oxygenation cannot be evaluated in ICUs. Predicting the risk of hypoxaemia during ETI and optimising pre-oxygenation are two major therapeutic goals. A reliable tool for assessing the quality of pre-oxygenation is therefore needed.

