# Study design AND CONDUCT

## Study schedule

Consecutive ICU patients requiring ETI will be randomly allocated to ETI with or without ORI monitoring before beginning of preoxygenation, with stratification by centre, expert or nonexpert intubator status (experts: ≥5 years’ ICU experience, or ≥1 year ICU experience plus ≥2 years’ anaesthesiology training) (24), and NIV or others devices for preoxygenation. Two intubators including at least one expert will be present throughout ETI. At least one of the intubators will be trained in ORI monitoring, i.e., will have attended an education session and used the device twice.

Randomisation will be via an electronic case-report form, using a balanced scheme with stratification as described above.

Informed consent will be obtained from the patient or next of kin.

Patients for whom no family member is available to receive information and consent to participate in the study within a time frame compatible with the study design will be included in the study after completion of an emergency consent form by the patient's attending physician. Informed consent will be sought from the patient upon regaining decision-making capacity.

Data collected:

- Patient characteristics: demographics, Simplified Acute Physiologic Score II, activity level (Knaus), Charlson comorbidity index, ICU admission diagnosis, reason for ETI, Sequential Organ Failure Assessment [SOFA] score, vital signs at enrolment, criteria for difficult face-mask ventilation, criteria for difficult intubation, and MACOCHA score
- Before, during ETI, and 2 minutes after successful ETI: ORI, Mallampati score, pre-oxygenation methods and duration, type and dosage of sedatives and neuromuscular blockers, Cormack-Lehane grade, glottic opening score, number of ETI attempts before success (each introduction of the laryngoscope into the mouth is a separate laryngoscopy attempt), with details: manoeuvres during laryngoscopy, reason for ETI failure, difficult ETI , duration of ETI , need for face-mask ventilation after first ETI attempt, need for gum elastic bougie, and types of life-threatening and other complications. Pulse oximetry will be recorded throughout the ETI procedure.
- Day 1 to 7: SOFA score
- Day 28: Mortality, ICU stay length, hospital stay length, cognitive score (F-TICS-m)

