### Statistical justification of the number of inclusions

Assuming a standard deviation of 10 at the lowest oxygen saturation in control group (33), no missing data, and cross-over for 5% of patients, with the two-sided alpha risk set at 0.05, including 950 patients will provide 85% power for detecting an absolute 2-percentage points between-group difference in lowest oxygen saturation (3% difference in FLORALI2 trial (12) and 96 vs 93% in PREVENT study (22)).

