### Randomisation

Randomization will be stratified by centre and expert or non-expert intubator status (experts: ≥5 years’ ICU experience, or ≥ 1 year ICU experience plus ≥2 years’ anaesthesiology training), preoxygenation devices (NIV, others).

It will be performed according to a 1:1 ratio and will be carried out in blocks.

The randomization will be performed under Ennov Clinical by connecting to the website: https://nantes-lrsy.hugo-online.fr/CSonline. The connection will be done with a login, a password and a study number, delivered by the data manager of the Research Unit of the CHU Nantes. The following information must be filled in:

- First initial of the name,

- First initial of the first name,

- Month and year of birth,

- Compliance with the inclusion and non-inclusion criteria (yes/no).

Randomization will be performed by the investigator after confirmation of the possibility of inclusion in the study. The inclusion number will be assigned automatically during randomization. An e-mail confirmation will be sent to the person who performed the randomization and to all the persons concerned.

The randomization list will be made by the statistician in charge of the study. An explanatory guide to randomization will be available online under Ennov Clinical.

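### The primary model is valid but adjusts only for the stratification factors; naming baseline predictors already collected would add precision at almost no cost

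*Protocol*

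**What the plan says.** Protocol section 7.2 (Analysis of primary endpoint) compares the lowest oxygen saturation between groups with a "linear mixed-effect regression model to take into account stratification variable (centre as random effect, intubator status (expert or non-expert) and preoxygenation device as fixed effect". These are the three stratification factors of the Randomisation section. The text names no further covariate.

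Three other places bear on the choice:

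- Section 1.1 (Positioning of the study) states: "Risk factors for potentially fatal hypoxaemia are hypoxaemia before ETI and/or difficult ETI (5").
- Section 5.1 (Study schedule) lists among the patient characteristics "reason for ETI, Sequential Organ Failure Assessment [SOFA] score, vital signs at enrolment, criteria for difficult face-mask ventilation, criteria for difficult intubation, and MACOCHA score". Section 6.2 adds BMI and individual airway criteria to the case report form.
- The subgroup list in section 7.2 includes BMI and reason for intubation (hypoxaemia or other), so the protocol already regards both as possibly relevant to the primary outcome.

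The sample-size section says that "including 950 patients will provide 85% power for detecting an absolute 2-percentage points between-group difference in lowest oxygen saturation". It rests on a standard deviation of 10, a "two-sided alpha risk set at 0.05", and "no missing data, and cross-over for 5% of patients". It gives neither the direction of the cross-over nor its denominator. No R-squared or correlation with the lowest saturation appears anywhere in the protocol.

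**The concern.** In a linear model the treatment coefficient is a difference in means whether or not baseline covariates are included. Adding prespecified prognostic variables measured before randomisation therefore leaves the estimand and the type I error as they were, and reduces the residual variance to the extent that those variables predict the outcome.

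The strata do not fully stand in for them. Intubator status describes the operator and says nothing of the patient's airway. The device stratum (NIV or other) reflects oxygen need only roughly, because device choice is left to the physician.

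What is at stake is the width of the primary confidence interval and some reserve of power, in a design whose stated power assumes no missing outcome data.

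**Working it through.** **Inputs from the protocol.** Total 950 patients; "It will be performed according to a 1:1 ratio", hence 475 per arm; difference 2 points; SD 10; two-sided alpha 0.05; 5% cross-over; stated power 85%.

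**Formula.** Normal approximation for two means: power = Phi(d / (SD × sqrt(2/n)) − 1.96), with n per arm.

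**Step 1: reproduce the stated 85%.** The standard error with 475 per arm is 10 × sqrt(2/475) = 0.649. The 5% can be read in several ways:

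- Ignored: 2/0.649 = 3.082; Phi(1.122) = 86.9%.
- Counted as loss of information: n = 475 × 0.95 = 451.25, standard error 0.666; 2/0.666 = 3.004; Phi(1.044) = 85.2%. In reverse, 85% power needs 449 per arm, 898 in total, and 898/0.95 gives 946, close to the planned 950.
- 5% of one arm crosses: effect 2 × 0.95 = 1.9; 1.9/0.649 = 2.928; Phi(0.968) = 83.4%.
- 5% of each arm crosses: effect 2 × 0.90 = 1.8; 1.8/0.649 = 2.774; Phi(0.814) = 79.2%. Reaching 85% would then need about 1110 patients.

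The stated figure is met, or nearly met, on every reading but the last.

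**Step 2: add covariates.** Let R² be the share of outcome variance explained by the added covariates beyond the stratification factors, taking 10 as the SD before they enter. The residual SD is 10 × sqrt(1 − R²): 9.747, 9.487 and 8.944 at R² of 0.05, 0.10 and 0.20. These R² values are assumptions. Putting each SD into the formula gives:

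| Reading of the 5% | R² = 0 | 0.05 | 0.10 | 0.20 |
|---|---|---|---|---|
| Loss (n = 451.25, effect 2) | 85.2% | 86.9% | 88.6% | 91.9% |
| Effect 1.9 | 83.4% | 85.2% | 87.0% | 90.6% |
| Effect 1.8 | 79.2% | 81.2% | 83.2% | 87.3% |

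For example, with effect 1.9 and R² = 0.20: 1.9/(8.944 × sqrt(2/475)) = 3.274; Phi(1.314) = 90.6%.

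**Step 3: the same gain in other units.** The confidence interval narrows by 1 − sqrt(1 − R²): 2.5%, 5.1% and 10.6%. The unadjusted sample size giving equal precision is 950/(1 − R²): 1000, 1056 and 1188.

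**Step 4: R² needed for 85% under dilution.** Solving for the residual SD gives 9.772 at effect 1.9, so R² = 1 − 0.9772² = 0.045. At effect 1.8 it gives 9.258, so R² = 0.143.

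**The case against.** The planned analysis is unbiased and reflects all three stratification factors. Extra covariates are a choice, and the protocol refers to a pre-defined analysis plan that is not shown. That stands as far as it goes: nothing here is wrong. But section 7.2 does state a covariate list, so improving that list is a fair comment on the document as written.

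A reader might infer that the trial is underpowered and that adjustment repairs it. The protocol does not support this. Only the 1.8-point reading falls well below 85%. ORI is withheld from investigators in the standard-care group, so cross-over mainly out of the ORI arm is plausible, which points to 1.9 points and 83.4%.

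A reader might also infer that the omitted predictors are strong. No figure supports that, and several facts argue for a modest gain:

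- Section 1.1 goes on to say that hypoxaemia during intubation is hard to predict, citing the same source as the risk factors.
- The risk-factor statement concerns potentially fatal hypoxaemia, not variation in the continuous lowest saturation.
- One of the two named factors, difficult intubation as it occurs, arises after randomisation and cannot be a baseline covariate.
- Entry requires SpO2 above 97% on oxygen, which limits the spread of enrolment SpO2.
- NIV is advised at higher oxygen flow, so the device stratum already carries part of baseline severity.

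Finally, the protocol does not say that every airway item is recorded before randomisation; section 5.1 lists the Mallampati score with data from before, during and after intubation. This restricts which values may be used, and the fix takes it into account.

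**Conclusion.** The point holds as a free improvement, not as an error. The primary model gives up some precision by ignoring baseline variables the trial already collects. Under each of the three cross-over readings in the table, an extra R² of 0.05 is worth about 2 percentage points of power, and 0.10 about 3 to 4. If the covariates turn out to predict nothing, the cost is a few degrees of freedom out of 950 patients.

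The size rests on an assumed R² beyond the stratification factors, on the protocol's SD of 10 and on a normal approximation. It does not rest on a power shortfall: without a direction and denominator for the cross-over, none is established, and adjustment cannot be said to restore a loss that may not exist.

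**What to change.** Before any comparison of outcomes by arm, add these fixed covariates to the primary model in section 7.2: reason for intubation (hypoxaemia or other), BMI as a continuous variable, and MACOCHA score. Enrolment SpO2 may be added, but little should be expected of it given the entry criterion.

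- Use only values recorded before randomisation, and confirm this for the MACOCHA score. Do not adjust for observed difficult intubation or for the ORI reached, since both arise after allocation.
- State a simple imputation rule for missing baseline values.
- Keep the stratification-only model as a supportive analysis.
- Align the Appendix 2 summaries, whose primary model omits the preoxygenation device.

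The cost is wording in the protocol and analysis plan. The variables are already collected, and no extra patient is needed.

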**Sensitivity analysis of primary endpoint**

The same analysis will be realized using the lowest oxygen saturation measured by local oximeter.

**Analysis of primary endpoint according to subgroup**

Primary endpoint will be analyzed according to pre-defined subgroups variables:

- - - Body mass index (<30 or ≥30)
    - Reason for ETI: hypoxaemia/other
    - Shock/No shock at inclusion
    - Difficult intubation (yes or no)
    - ORI threshold (<0.6 or ≥0.6)

**Analysis of secondary endpoints**

All analyses will be adjusted on stratification criterion.

- Occurrence of at least one severe life-threatening complication: death, cardiac arrest, arterial systolic pressure <90 mmHg, and/or SpO_2_<80% and occurrence of each one using logistic mixed-effect regression model.

- The rates of death in ICU and at 28 days will be calculated via Kaplan-Meier plots and compared between groups using Cox regression models.

- ICU and hospital length of stay will be compared using Fine and Gray model to take into account death as competing risk.

- Cognitive score evaluated by F-TICS-m will be compared between groups using linear mixed effect regression model. Patients dead at day 28 will be not included on this analysis.

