## Recruitment modalities

The recruitment will be done within the ICU departments of the centers participating in the study. It is planned to include 950 patients admitted to the intensive care unit and justifying an orotracheal intubation procedure, after reading the information letter and collecting the consent of the patient or the trusted person, or carrying out the emergency inclusion procedure. In the last two cases, the patient's consent will be collected posteriori after reading the information letter. Patient will be followed until day 28 or death.

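### At the low end of the protocol's own event rates, the mixed logistic model prescribed for peri-intubation death and cardiac arrest can separate or be very unstable; a sparse-event method should be prespecified for these two components

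*Protocol*

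**What the plan says.** Under Analysis of secondary endpoints (section 7.2), the protocol takes the composite of death, cardiac arrest, systolic pressure below 90 mmHg and SpO2 below 80%, "and occurrence of each one using logistic mixed-effect regression model". The protocol summary in Appendix 2 repeats this. The same section requires adjustment of all secondary analyses for the stratification factors, which are centre, intubator status and preoxygenation device (Randomisation). A random centre effect is written out only for the primary endpoint model. It is the natural reading here, because no other random effect is named, but it is an inference.

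Section 1.1 (Positioning of the study) gives background complication rates: 25% each for severe hypoxaemia and severe hypotension, then "cardiac arrest (1-3%), and death (0.5-3" per cent. On size, Recruitment modalities states "It is planned to include 950 patients", Randomisation states "It will be performed according to a 1:1 ratio", and Appendix 2 foresees 20 centres. The protocol gives no expected event counts for the rare components and no alternative if the model cannot be fitted.

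**The concern.** A logistic model with arm, two binary covariates and a random intercept over 20 centres is reasonable for about 240 events (950 x 25% = 237.5). With five or ten events, one arm or one level of a covariate may have no event. The maximum-likelihood coefficient is then infinite (separation), and its Wald test and interval are meaningless. Short of that, the odds ratio can be far from 1 by chance alone.

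Safety is a stated secondary objective, and death and cardiac arrest are its gravest components. If the prescribed model fails, a replacement has to be chosen after the data have been seen, in an open-label trial whose section on changes to the analysis strategy says that none are planned.

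**Working it through.** **The plan's own figure.** The only power statement concerns the primary endpoint: "including 950 patients will provide 85% power" for "detecting an absolute 2-percentage points between-group difference in lowest oxygen saturation", "with the two-sided alpha risk set at 0.05". With SD 10 and 475 per arm, SE = 10 x sqrt(2/475) = 0.649. For a difference of 2, 2/0.649 - 1.96 = 1.12, which gives 86.9% power. For 1.9 (2 x 0.95 for 5% cross-over) power is 83.4%. The stated 85% is reproduced to within 2 points. It says nothing about rare binary components, so those are worked out below.

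**Expected events** (950 x rate):
- Death: 950 x 0.005 = 4.75 to 950 x 0.03 = 28.5.
- Cardiac arrest: 950 x 0.01 = 9.5 to 28.5.
- Per centre (20 centres): 0.24 to 1.4. At 0.5%, about 16 of 20 centres have no event.

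**Chance that at least one arm has no event**, no true effect. With z = (1 - p)^475, the chance is 1 - (1 - z)^2.
- p = 0.5%: z = 0.0925, chance 17.6%.
- p = 1%: z = 0.0084, chance 1.7%.
- p = 2%: z = 0.00007, chance 0.01%. At 3% it is negligible.
- If the ORI arm's rate were half the control rate: 0.0925 + 0.3045 - 0.0925 x 0.3045 = 36.9% at 0.5%, and 10.0% at 1%.

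**Chance that any coefficient separates.** This needs covariate shares that the protocol does not give. A random-intercept logistic model was simulated with no treatment effect, 20 centres and between-centre SD 0, 0.5 or 1 on the logit scale.
- 50% expert, 35% NIV: 32-35% at 0.5%, 6-11% at 1%, none in 400 runs at 2%, none at 3%.
- 30% expert, 20% NIV (run at 0.5% and 3% only, SD 0.5): 54% and 0.3%.

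A direct calculation without centre effects agrees. Given n events, the chance of no separation is the product over the three factors of 1 - q^n - (1 - q)^n, where q is the share in one level. Averaged over n ~ Binomial(950, p), the 50%/35% shares give 37% at 0.5% and 6% at 1%. The 30%/20% shares give 55%, 20% and 2.5% at 0.5%, 1% and 2%. The 6-11% range at 1% therefore belongs to the 50%/35% shares and would be higher with more uneven ones.

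**Precision.** With a = 475p events per arm, SE of the log odds ratio = sqrt(2 x (1/a + 1/(475 - a))).

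| Rate | Events | SE | 95% CI: OR times or divided by | Simulated null ORs above 3 or below 1/3 (50%/35% shares) |
|---|---|---|---|---|
| 0.5% | 4.75 | 0.92 | 6.1 | 31-38% |
| 1% | 9.5 | 0.65 | 3.6 | 14-20% |
| 2% | 19 | 0.46 | 2.5 | 4.5% |
| 3% | 28.5 | 0.38 | 2.1 | 1-2% |

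**The alternative.** Firth-penalised logistic regression with arm, intubator status and device converged in 1000 of 1000 simulated trials at each of 0.5%, 1% and 3%. The 95% spread of its null odds ratios was 0.14-7.4, 0.23-3.8 and 0.45-2.1.

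**The case against.** The case against rests on five arguments.

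- **The ranges run to 3%.** A reader might infer that the protocol's rates leave too few events to fit the model at all. They do not. At 2-3% the arm odds ratio is estimable, and even at 1% an empty arm is rare. The serious problem is death near the bottom of its range. This stands and limits the point.
- **Separation is not always loss of the arm effect.** At 0.5%, roughly half or more of the separation comes from intubator status or device alone, when the arm odds ratio generally stays finite. The relevant figure for the treatment comparison is the 18%. A centre variance estimated as zero is also no failure, because the model then reduces to ordinary logistic regression. Both stand.
- **False alarms.** A reader might infer an inflated error rate from the extreme odds ratios. No such rate has been shown for the prescribed model. An unadjusted 2x2 Wald test with 475 per arm, counting an empty arm as non-significant, rejects in 0.15% of null trials at 0.5% and 1.7% at 1%. That is conservative.
- **Other results carry safety too.** The composite is dominated by the common components, and mortality is analysed separately in ICU and at 28 days. This limits the stakes.
- **It could be left to the SAP.** A fallback may exist in a SAP that is not shown. But the protocol does not leave the method open: it names a model for each component, and that model may not be estimable at rates it quotes itself.

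The low end is also plausible here, though the protocol does not quantify it. Peri-intubation data are collected only to 2 minutes after successful intubation. Patients without time to randomise, for instance because of cardiac arrest, are not included. Emergency inclusions who die before any consent is obtained are dropped from the analysis.

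**Conclusion.** The point holds as a cheap improvement to two secondary safety analyses. If peri-intubation death runs near 0.5% (about 5 events), the prescribed model has about an 18% chance of yielding no finite arm odds ratio. About a third of simulated null odds ratios lie beyond three-fold. If cardiac arrest runs near 1% (about 10 events), the chance of an empty arm is about 2%, and the interval spans a factor of 3.6 either way. At 2-3% the model is serviceable. The primary endpoint, the composite and the two common components are untouched.

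The empty-arm figures need only the protocol's rates, 475 patients per arm and no true effect. The figures for separation of any coefficient also rest on assumed expert and NIV shares, and the simulated ones on an assumed between-centre SD. Application of the random centre effect to these endpoints is inferred from the primary model.

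**What to change.** Keep the mixed logistic model for the composite, systolic pressure below 90 mmHg and SpO2 below 80%. For peri-intubation death and cardiac arrest, state in advance that the main result is the count per arm and the risk difference with an exact or score-type 95% CI. If an adjusted odds ratio is wanted, specify Firth-penalised logistic regression with arm, intubator status and device, without a centre effect. Make the same change in section 7.2 and in the Appendix 2 summary.

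The cost is a sentence or two before the data are seen. The two rare components would no longer be adjusted for centre. The change gives finite, valid estimates but cannot make up for few events: power to detect a halving is about 9% at 0.5%, 14% at 1% and 34% at 3%, so these results should be read as descriptive.

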### Secondary endpoint(s)

- Sensitivity analysis of primary endpoint
  - Lowest oxygen saturation, measured by local oximeter, during the interval between the first laryngoscopy (defined as introduction of the laryngoscope into the mouth) and the end of the second minute after successful ETI.
- Sub-group analysis of primary endpoint
  - Lowest oxygen saturation in pre-defined subgroups
    - Body mass index (<30 or ≥30)
    - Reason for ETI: hypoxaemia/other
    - Shock/No shock at inclusion
    - Difficult intubation (yes or no)
    - ORI threshold (<0.6 or ≥0.6)

- Safety outcome

- - Occurrence of at least one severe life-threatening complication: death, cardiac arrest, arterial systolic pressure <90 mmHg, and/or SpO_2_<80% and occurrence of each one.

- Efficacy outcome

- - ICU mortality
  - 28-day mortality
  - ICU and hospital stay length
  - Mean cognitive score at day 28 between two groups (modified Telephone Interview for Cognitive Status (F-TICS-m) (23)

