| **Statistical analysis** | Statistical analyses will be performed by a biostatistician from the methodology and biostatistics platform using SAS or R or Stata.  A data review will be carried out before the freezing of clinical trial data bases, and statistical analyses, with the main stakeholders in the study (investigator, CRA, data manager and biostatistician…). The objective of this review will be to take stock of any difficulties encountered during the study, and to classify the different deviations in order to define the analysis populations.  **Description of the groups at baseline**  Baseline characteristics will be studied using descriptive statistics. No statistical tests will be performed.  **Analysis of primary endpoint :**  Lowest oxygen saturation measured using MASIMO oximeter, during the interval between the first and the end of the second minute after successful ETI (32) will be compared between groups using linear mixed-effect regression model to take into account stratification variable (centre as random effect, intubator status (expert or non-expert) as fixed effect).  **Sensitivity analysis of primary endpoint**  The same analysis will be realized using the lowest oxygen saturation measured by local oximeter.  **Analysis of primary endpoint according to subgroup**  Primary endpoint will be analyzed according to pre-defined subgroups variables:   - Body mass index (<30 or ≥30) - Reason for ETI: hypoxaemia/other - Shock/No shock at inclusion - Difficult intubation (yes or no) - ORI threshold (<0.6 or ≥0.6)   **Analysis of secondary endpoints**  All analyses will be adjusted on stratification criterion.   - Occurrence of at least one severe life-threatening complication: death, cardiac arrest, arterial systolic pressure <90 mmHg, and/or SpO_2_<80% and occurrence of each one using logistic mixed-effect regression model. - The rates of death in ICU and at 28 days will be calculated via Kaplan-Meier plots and compared between groups using Cox regression models. - ICU and hospital length of stay will be compared using linear mixed-effect regression models. - Cognitive score evaluated by F-TICS-m will be compared between groups using linear mixed effect regression model. Patients dead at day 28 will be not included on this analysis. |

SUMMARY OF PROTOCOL IN FRENCH

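### Kaplan-Meier and Cox are prescribed for ICU death with no rule for patients discharged alive; if discharge is censored, as is usual, ICU mortality is overstated

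*Protocol*

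**What the plan says.** Section 2.2 lists "ICU mortality" among the efficacy outcomes, separately from 28-day mortality. Section 7.2, under the analysis of secondary endpoints, gives both the same treatment: "The rates of death in ICU and at 28 days will be calculated via Kaplan-Meier plots and compared between groups using Cox regression models". The English summary in Appendix 2 repeats this. Neither place says what happens to a patient who leaves the ICU alive.

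The next item in the Section 7.2 list covers length of stay: "ICU and hospital length of stay will be compared using Fine and Gray model to take into account death as competing risk". On follow-up, Section 4.4 states: "Patient will be followed until day 28 or death". Observation therefore continues past ICU discharge, and Section 5.1 has mortality and both lengths of stay collected at day 28.

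**The concern.** Death in the ICU and live discharge from the ICU are competing events: whichever comes first rules out the other. Kaplan-Meier with discharge treated as censoring assumes that discharged patients would have gone on to die in the ICU at the same rate as those still there. Its complement then describes a hypothetical ICU that nobody leaves alive. It is not the share of patients who die in the ICU, which is what a reader takes an ICU death rate to mean.

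Two results are at stake. The reported ICU mortality in each arm would be too high. The Cox hazard ratio would describe the rate of death among patients still in the ICU, and that can differ from the between-arm difference in the risk of dying there. The length-of-stay rule already recognises that death and discharge compete, but the mortality rule has no counterpart.

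**Working it through.** **Figures in the plan.** The protocol states no ICU death rate, length of stay or power for mortality. Its only computed figure is the 85% power for the primary endpoint, from "Assuming a standard deviation of 10 at the lowest oxygen saturation in control group" and an "absolute 2-percentage points between-group difference in lowest oxygen saturation". With 475 per arm, power = Φ(δ/(10·√(2/475)) − 1.96). This gives 86.9% for δ = 2 and 85.2% for δ = 1.95 (one simple allowance for the 5% cross-over). The figure reproduces and has no bearing on this point.

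**Set-up (all rates assumed).** Constant daily hazards, h_d for ICU death and h_a for live discharge:
- True ICU death risk by day t: CIF(t) = h_d/(h_d + h_a) × (1 − exp(−(h_d + h_a)t))
- One minus Kaplan-Meier with discharge censored: 1 − exp(−h_d·t)

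**Main example: 25% dead in the ICU and 65% discharged alive by day 28, so 10% still there.**
- Total hazard = −ln(0.10)/28 = 0.0822 per day
- h_d = (0.25/0.90) × 0.0822 = 0.0228 per day
- One minus Kaplan-Meier at day 28 = 1 − exp(−28 × 0.0228) = 47%, against a true 25%

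**Other death rates.**
- Death plus discharge held at 90%: 20% becomes 1 − exp(−(0.20/0.90) × 2.303) = 40%, and 30% becomes 1 − exp(−(0.30/0.90) × 2.303) = 54%.
- Discharge held at 65% instead: 20% becomes 1 − exp(−(0.20/0.85) × 1.897) = 36%, and 30% becomes 1 − exp(−(0.30/0.95) × 2.996) = 61%.

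**A second parameterisation: eventual ICU mortality and mean ICU stay assumed.** Entries are true cumulative incidence versus one minus Kaplan-Meier at day 28.

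| Eventual ICU mortality | Mean stay 7 days | 10 days | 14 days |
|---|---|---|---|
| 20% | 19.6% vs 55.1% | 18.8% vs 42.9% | 17.3% vs 33.0% |
| 30% | 29.5% vs 69.9% | 28.2% vs 56.8% | 25.9% vs 45.1% |
| 40% | 39.3% vs 79.8% | 37.6% vs 67.4% | 34.6% vs 55.1% |

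The overstatement runs from a factor of 1.6 (55.1/34.6) to 2.8 (55.1/19.6), or from 15.7 points (33.0 − 17.3) to 40.5 points (79.8 − 39.3).

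**The comparison between arms.** In the main example, raise the discharge hazard in one arm by 30% and leave h_d unchanged. Discharge hazard = 0.0594 × 1.3 = 0.0772 and total = 0.1001, so CIF(28) = (0.0228/0.1001) × (1 − exp(−28 × 0.1001)) = 21.4%. ICU mortality differs, 25% against 21.4%, while the cause-specific hazard ratio is 1.

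Simulation with 475 per arm and 4,000 runs, control hazards 0.03 (death) and 0.07 (discharge), 5% level and follow-up to day 28. The log-rank test serves as the score test of the Cox model.

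| Scenario | Log-rank rejects | Two-proportion test rejects |
|---|---|---|
| Identical arms | 5.1% | 5.3% |
| Same death hazard, discharge 1.3 times faster in one arm | 5.4% | 31.3% |
| Both hazards 1.3 times higher in one arm (eventual ICU mortality 30% in both) | 56.2% | 5.6% |

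In rows two and three each test responds correctly to its own quantity. The quantities differ.

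**The case against.** **The censoring rule is inferred.** The protocol does not say that patients are censored at ICU discharge. It follows them to day 28 and refers to a pre-defined analysis plan, not available here, which could set the rule. If discharged patients stayed in the risk set to day 28 as free of ICU death, with complete follow-up, one minus Kaplan-Meier would equal the cumulative incidence and Cox would become a subdistribution comparison. This stands as a reason to word the point conditionally. It does not remove it, because the protocol nowhere describes that handling and censoring is the ordinary application of the methods it names.

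**Cox with discharge censored is not invalid.** A reader might infer that the planned test addresses the wrong quantity. That goes too far: it validly compares cause-specific hazards, a recognised target under competing risks. The error lies in the absolute rate. For the comparison, the issue is that the hazard ratio need not track the ICU death risk.

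**A difference in the ICU proportion can be misleading too.** When discharge is faster and the death hazard unchanged, fewer patients die in the ICU only because they leave sooner. Nothing in that example shows fewer deaths overall. The 30% faster discharge is purely illustrative; the protocol, with its one-hour treatment period, offers no support for an effect of that size. This objection stands and is why the ICU result should be read beside 28-day mortality.

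**Fine and Gray for length of stay does not contradict the mortality sentence.** Agreed. It shows that the two rules are not aligned and supports the point without proving it.

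**Conclusion.** The point holds in conditional form. The protocol fixes Kaplan-Meier and Cox for ICU death and gives no rule for live discharge. Under the usual censoring, the reported ICU death rate exceeds the proportion who die in the ICU. The direction needs no assumed rate, only that discharges occur while deaths are still accruing. The size rests wholly on assumptions: 47% instead of 25% in the main example, and a factor of about 1.6 to 2.8 over eventual ICU mortality of 20% to 40% and mean stays of 7 to 14 days, all under constant hazards.

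The documents do not support extending this to 28-day mortality, where the planned methods are sound, or to the primary endpoint or the sample size. ICU mortality is one secondary endpoint. The change is still worth making because the published figure could be badly off and the repair is small.

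**What to change.** In Section 7.2 and the Appendix 2 summaries, restrict Kaplan-Meier and Cox to 28-day mortality. For ICU mortality, set the horizon at day 28, where follow-up ends, and choose one of two routes:
- the proportion of analysed patients who die in the ICU by day 28, compared with the logistic mixed model already planned for the complication endpoint; or
- cumulative incidence with live ICU discharge as the competing event, compared by Fine and Gray, with the cause-specific hazard ratio alongside.

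State that the ICU result is interpreted together with 28-day mortality, because ICU mortality also depends on when patients are discharged.

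Align the summaries at the same time. The English one still says "ICU and hospital length of stay will be compared using linear mixed-effect regression models" where the main text has Fine and Gray, and the French one pairs Kaplan-Meier for mortality with a linear mixed model.

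The cost is about one sentence in the protocol, carried into the SAP, plus the summary corrections. No new data are needed and the sample size does not change.
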